### Missing data

Information collected during the study related to reasons that values are missing will be helpful in examining assumptions about missing data, e.g., whether data are missing completely at random (MCAR), missing at random (MAR), or missing not at random (MNAR). In general, all available data will be used in estimation and inference. Following the recommendations of the 2010 National Academy of Sciences report on the treatment of missing data in clinical trials, sensitivity analyses will be carried out to explore the effect of missing outcomes on inference for the primary outcomes. Multiple imputations will be used under MCAR and MAR assumptions. In the presence of informative censoring, shared parameter random effects models and/or pattern mixture models will be fit, and sensitivity analyses will be performed to check the robustness of study conclusions.

## Heterogeneity of treatment effects

We will test for heterogeneity of treatment effect as a follow-on exploratory analysis whenever a main treatment effect is detected, to determine whether the intervention has different relative benefits for different subgroups. ***Subgroup analyses***. We anticipate treatment effects will vary across different patient subpopulations defined by the following cofactors: age subcategories (< 80 vs. ≥ 80 years old at the time of enrollment) [11], sex [36–38], race [39, 40], place of residence at the time of enrollment (nursing home residence vs. other) [41], presence or absence of previous AV access creation [42, 43], and location of study AV access placement (forearm or arm) [15, 44−46]. Thus, subgroup analyses will be performed, and the tests will be based on the coefficients for the interaction terms between the intervention and the subpopulation cofactors.

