**Discussion:**

In the absence of studies using robust and unbiased research methodology to address vascular access care for hemodialysis patients, clinical decisions are limited to inferences from observational studies. The goal of the AV Access Study is to generate evidence to optimize vascular access care, based on objective, age-specific criteria, while incorporating goals of care and patient preference for vascular access type in clinical decision-making.

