## Eligibility criteria

These are listed in Table 2. Medical suitability for AV access surgery will be determined according to regional standard care for each patient. Anatomic and surgical suitability for AVF creation or AVG placement will be determined by the vascular access surgeon, according to usual care.

**Table 2 Tab2:** Eligibility criteria

Inclusion criteria
1. Are of age 60 years or older
2. Have ESKD
3. Receive in-center HD as treatment for ESKD
4. Have CVC as the vascular access used for HD at the time of referral for AV access creation
5. Were referred by patient’s treating medical providers for placement of AV access
6. Have at least one of the following comorbid conditions: cardiovascular disease, peripheral vascular disease, and/or diabetes mellitus
7. Receive care for ESKD at medical facilities whereby the research team will have access to medical information (inpatient medical chart, outpatient medical chart, dialysis medical chart, outpatient interventional nephrology or interventional radiology procedures) during the study
8. Were evaluated by vascular access surgery and have native vasculature deemed preoperatively to be suitable for surgical creation of either type of AV access (AVF or AVG) in an upper extremity in the opinion of the surgeon
9. Are scheduled or will be scheduled for AV access surgery in an upper extremity, based on the plans developed by treating medical providers
10. Provide informed consent for study participation (for candidates with adequate consent capacity based on Consent Capacity Assessment tool) or obtain informed consent for study participation from a Legally Authorized Representative (for candidates unable to consent based on Decision-Making Capacity Assessment tool)

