## Statistical methods

### Sample size calculation and power considerations for primary outcome

The sample size estimate is based on the primary hypothesis that, by the end of the study, the patients in the AVG group will have more CVC-free days than patients in AVF group. Based on our pilot study [19, 20, 30], the average rate for CVC-free days was 15/100 patient-days among study patients who underwent AVF placement; similar or higher rate of CVC-free days was reported in other studies [31–33]. For this study, sample size calculations are based on two-sided tests with 5% type 1 error rate and a conservative estimate of 25% drop-out rate. Assuming a Poisson distribution and an average follow-up of two years, we will have > 90% power to detect a minimum of 5% points increase in CVC-free days in the graft group with 131 patients per group. We also considered situations where overdispersion is present for CVC-free days. With a total sample of 262 and 15/100 patient-days in the fistula group, we will have 80% power to detect an effect size of 25% for a 5% inflation of variance. The power will be greater if the rate of CVC-free days is 20/100 patient-days or higher in the fistula group.

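### The article names only one form for effect modification by age, a split at 80 years; adding a continuous-age interaction would be a cheap improvement

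*Protocol article*

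**What the plan says.** All references are to the protocol article; no separate analysis plan is at hand.

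- **Form of age.** The section Heterogeneity of treatment effects lists six cofactors. Age enters as "age subcategories (< 80 vs. ≥ 80 years old at the time of enrollment", with a literature reference attached. No continuous, spline or multi-category version of the age interaction appears in the article.
- **Test.** For all six cofactors, "the tests will be based on the coefficients for the interaction terms between the intervention and the subpopulation cofactors".
- **Status.** The work is done "as a follow-on exploratory analysis whenever a main treatment effect is detected".
- **Population.** Table 2 requires that participants "Are of age 60 years or older" and sets no upper limit.
- **Aim.** The Discussion paragraph of the abstract says that the evidence should serve to optimize access care "based on objective, age-specific criteria, while incorporating goals of care and patient preference for vascular access type in clinical decision-making".
- **A contrast.** Under Analysis for exploratory outcomes, the physical function score is dichotomized at the median, but continuous and tertile versions are added. Age receives no such addition.

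**The concern.** A single cut at 80 in a population that starts at 60 has two effects. It places a 61-year-old and a 79-year-old in the same cell, so a gradient between those ages cannot contribute to the test. It also rests the contrast on however many participants are 80 or older, who may be few out of 262. The section itself expects effects to differ across its cofactors, and the abstract speaks of age-specific criteria. If the difference between graft and fistula drifts gradually with age, the named test may well fail to show it, and a non-significant interaction could then be taken as a sign that age does not matter.

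**Working it through.** **No figure to reproduce.** The article states no expected mean or SD of age, no share aged 80 or over, and no power for any interaction. Everything below therefore rests on assumed age distributions.

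**Inputs from the article.** Total sample 262 and two-sided 5% tests (Sample size calculation and power considerations for primary outcome); 1:1 allocation (Randomization); lower age limit 60 (Table 2); cut at 80 (Heterogeneity of treatment effects).

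**Step 1: information kept by the cut.** Suppose the log rate ratio is linear in age. The efficiency of the split relative to a linear treatment-by-age term is then the squared correlation between age and the indicator of age ≥ 80:

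r² = p(1 − p)d² / s²

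Here p is the share aged ≥ 80, d is the difference in mean age between the two cells, and s is the SD of age.

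Example: normal ages with parent mean 72 and SD 8, truncated to 60–95. This gives p = 0.168 (44 of 262), s = 6.95, and mean ages 84.03 and 70.84, so d = 13.19.

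r² = 0.168 × 0.832 × 13.19² / 6.95² ≈ 24.3 / 48.3 ≈ 0.50

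About half the information is lost.

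**Step 2: range over assumed distributions.** For uniform ages the formula reduces to 3p(1 − p). The power column is Φ(2.802√r² − 1.960), the power of the split when the continuous test would have 80%.

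| Assumed ages | Share ≥ 80 | Number of 262 | Kept | Lost | Power of split |
|---|---|---|---|---|---|
| Truncated normal 68/6 | 2.5% | 7 | 17% | 83% | 21% |
| Truncated normal 70/7 | 8.3% | 22 | 35% | 65% | 39% |
| Truncated normal 72/8 | 16.8% | 44 | 50% | 50% | 51% |
| Truncated normal 74/8 | 23.3% | 61 | 56% | 44% | 56% |
| Truncated normal 78/8 | 39.6% | 104 | 65% | 35% | 62% |
| Uniform 60–85 | 20% | 52 | 48% | 52% | 49% |
| Uniform 60–90 | 33% | 87 | 67% | 33% | 63% |
| Uniform 60–95 | 43% | 112 | 73% | 27% | 67% |
| 60 + exponential, mean excess 7 | 5.4% | 14 | 47% | 53% | 49% |
| 60 + exponential, mean excess 11 | 13.9% | 37 | 63% | 37% | 60% |

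(Truncated-normal labels are parent mean/SD on 60–95; the exponentials are cut off at 100.)

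The loss runs from about 27% to 83%. It is half or more when ages are near truncated normal with about 17% or fewer aged ≥ 80, for uniform 60–85, and for the exponential with mean excess 7. It is below half for older cohorts and for the more spread-out skewed shape.

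**Step 3: precision of the split itself.** With equal allocation in each cell, the variance of the interaction contrast divided by that of the main effect is 1/p + 1/(1 − p) = 1/[p(1 − p)]. At p = 0.10, 0.15 and 0.20 (26, 39 and 52 participants) this is 11.1, 7.8 and 6.2.

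**Step 4: the opposite truth.** The squared correlation is symmetric. If the effect really jumps at 80 and is flat elsewhere, the split loses nothing, and the linear term keeps only the share in the Kept column.

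**The case against.** The best defence is that nothing here is wrong or contradictory. The cut is prespecified and sourced, it is tested by an interaction rather than by comparing subgroup p-values, and the analysis is labelled exploratory and conditional on a main effect. All of this stands and limits the weight of the point. Without the cited source, nobody can say from the article that 80 is an arbitrary threshold.

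A second defence is that the article condenses a fuller plan, which might add a continuous version. That is possible, so the claim is only that the article names this one form. But a form and a test are stated, so the point concerns a choice made and not an omitted detail.

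Third, a reader might infer that effect modification by age is an objective of the trial. The documents do not support that. The phrase "based on objective, age-specific criteria" occurs in one abstract sentence, and restricting enrollment to people aged 60 or over may be all it means. Neither the Objectives, Table 1 nor the three closing questions ask how the effect varies within that range. The phrase makes a good age analysis more useful; it does not make it a main aim.

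Finally, a continuous term would still be an exploratory interaction test in 262 people. It improves the chance of seeing a gradient but does not make the trial powered for one.

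**Conclusion.** The point holds as a cheap improvement. Used alone, the split at 80 is an inefficient way to look for gradual change with age in a population starting at 60. The loss is roughly 25% to 80% of the information, and about half in the truncated-normal case with about 17% aged 80 or over. This rests on two assumptions that the article does not supply: the age distribution, and a log rate ratio that is linear in age.

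Two stronger readings should be resisted. One is that at least half the age information is certainly thrown away: several plausible age distributions give losses of 27% to 44%, and a true step at 80 gives none. The other is that a null interaction is bound to mislead: the article does not say that it will treat a null as evidence of no modification, and it calls the analysis exploratory. The risk lies in how a null would be reported, which one sentence can settle.

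**What to change.** Add to Heterogeneity of treatment effects, or to the analysis plan:

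1. Test the treatment-by-age interaction with age at enrollment as a continuous variable, linear in the log rate ratio, with a spline as a check on shape.
2. Plot the estimated rate ratio with its confidence band across age.
3. Keep the < 80 and ≥ 80 estimates, with confidence intervals and the number of participants in each group, as a display.
4. State that a non-significant age interaction will be reported as inconclusive, not as showing no difference by age.

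The cost is a few lines of text. Age at enrollment is already needed for eligibility and for the existing split, so no new data should be required. The article describes the trial as still enrolling; if that is so, the change can be fixed before results are known. The downside is that a linear test is less sensitive to a sharp step at 80, which the spline and the retained split cover.

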## Randomization

After informed consent is obtained, a member of the study team at each clinical center enacts the randomization through the centralized REDCap platform (Fig. 1). The randomization system is based on a block-permutation scheme with variable (two to four) block sizes, and assigns participants in a 1:1 ratio to AVG or AVF placement, stratified by (a) clinical center and (b) history of previous AV access surgery.

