## Interventions

The study intervention is surgical placement of an AV access in an upper extremity (referred to as index AV access), either an AVF or an AVG, according to randomized allocation. Both types of AV access surgery are considered standard care. The specific vasculature used for index AVF or index AVG is at the discretion of the treating surgical team. The sites will use Food and Drug Administration (FDA)-approved grafts, with most common material being expandable polytetrafluoroethylene (ePTFE) grafts. Scheduling of the index AV access surgery date will occur according to local practices.

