### Adherence to allocated intervention of index AV access surgery

After informed consent is obtained, the randomization assignment (i.e., type of index AV access to be surgically created) will be relayed to the vascular surgery team through verbal and electronic mail communication. Surgical intervention adherence to the assigned, index AV access is monitored during the study. All events of index AV access surgery postponement, missed surgery, or cancellation, with or without rescheduling, will be recorded along with the reason for such events.

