## Data collection

The schedule of assessments is summarized in Table 3. Participant’s baseline physical function will be assessed with objective tests (i.e., Grip Strength [26] and Chair stand [27]) and subjective instruments (i.e., Pepper Assessment Tool for Disability [28] and Clinical Frailty Scale [29]). Data will be collected prospectively through monthly review of electronic medical records for events documented at outpatient dialysis units, outpatient clinics, outpatient or inpatient interventional nephrology/interventional nephrology, and inpatient charts. We will record receipt of allocated index AV access (date of surgery, type of AV access surgery performed [AVF or AVG] and anatomical description, and attending surgeon’s expertise [number of new AV access surgeries performed in the 12 months prior to study start-up]). Medical events of interest, listed in **Additional file 7**, will be recorded with the diagnoses deemed by the treating medical team. Questionnaires will be administered pre-randomization and during follow-up at months 6, 12, 18 and 24 via telephone interviews. Time points for questionnaires administration are calculated from the date of randomization. The type(s) of vascular access a patient has at the time of questionnaire administration will be documented as either CVC, index AV access, and/or new AV access. At each clinical center, study coordinators responsible for questionnaire administration and data collection have received in-depth training in all study-related operational procedures, data collection, and data entry. Events of major or non-major protocol deviation and drop-out will be monitored and recorded (**Additional file 8**).

**Table 3 Tab3:** Schedule of Evaluations

Assessment	Pre- & Screening	Baseline at randomization	Study Surgery	Schedule in Months			
				M6	M12	M18	M24
Medical history*	X	X					
Duplex ultrasound of vessels, pre-op^£^	X						
Consent Capacity Assessment		X					
Informed consent		X					
Demographics*	X						
Living situation		X					
Highest scholastic education achieved		X					
Medical Insurance*		X					
Nephrology care background*		X					
Medications*		X					
Blood laboratory data*		X (monthly)					
End-stage kidney disease history*	X						
Past AV access history*		X					
CVC history*		X					
Randomization group		X					
Surgeon expertise			X				
Index AV access description			X				
Antibiotic administered peri-op			X				
Grip Strength^†^		X					
Chair Stand test^†^		X					

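### The forearm-or-arm subgroup uses a site chosen after randomization by surgeons who know the assigned access, so its interaction test lacks randomization's protection and may be biased

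*Protocol article*

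**What the plan says.** The section on heterogeneity of treatment effects in the protocol article names six cofactors and bases each test on the interaction between intervention and cofactor. Age and place of residence are tied to enrollment; sex, race and previous access creation are also baseline traits. The sixth is "location of study AV access placement (forearm or arm"), with no time anchor.

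Other sections give the order of events:

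- Randomization: "After informed consent is obtained, a member of the study team at each clinical center enacts the randomization". Allocation is "stratified by (a) clinical center and (b) history of previous AV access surgery", so site is not a stratification factor.
- Adherence to allocated intervention: the assignment "will be relayed to the vascular surgery team through verbal and electronic mail communication".
- Interventions: "The specific vasculature used for index AVF or index AVG is at the discretion of the treating surgical team".
- Data collection: what is recorded on receipt of the index access includes "type of AV access surgery performed [AVF or AVG] and anatomical description". Table 3 puts the description of the index access in the study-surgery column.
- Adherence section again: "All events of index AV access surgery postponement, missed surgery, or cancellation, with or without rescheduling, will be recorded", so the plan foresees randomized participants without an index access.

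Inclusion criterion 8 (Table 2) requires vessels suitable for either access type in an upper extremity. It fixes no site.

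**The concern.** A subgroup factor supports a randomized comparison within its levels only if it is fixed before allocation or cannot be affected by it. Here the access type is known when the vessels are selected, and the vessels that suit a fistula need not be those that suit a graft. Forearm patients in the fistula group and forearm patients in the graft group may therefore be different kinds of patient. The interaction coefficient would then mix any real effect modification with the way site was chosen.

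At stake is a site-specific statement, such as one access type doing better in the forearm and the other in the arm. Readers could take it as randomized evidence when it is partly or wholly selection. Participants who never have surgery have no forearm-or-arm value, so this one model also loses randomized participants for a reason that arises after allocation.

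**Working it through.** The plan states no figure for this subgroup, so there is none to reproduce. The check has three parts.

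**1. Order of events.** Consent, then randomization, then the assignment sent to the surgical team, then choice of vessels at that team's discretion, then recording of the anatomy. Each step is stated in the sections cited above. Site is therefore a post-randomization variable chosen with knowledge of the assigned group. The article names no planned site recorded before allocation.

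**2. A case that can be checked by hand (assumed inputs, no treatment effect).** Only the average rate of 15 CVC-free days per 100 patient-days comes from the article (the planning value for fistulas). Assume half the patients have good veins and half poor, with rates in the ratio 5:3 around that average: 18.75 and 11.25, mean (18.75 + 11.25)/2 = 15. Assume fistulas go in the forearm only when veins are good, and graft site is unrelated to vein quality.

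- Forearm: fistula 18.75, graft 15; difference -3.75; rate ratio 15/18.75 = 0.80.
- Arm: fistula 11.25, graft 15; difference +3.75; rate ratio 15/11.25 = 1.33.
- Apparent interaction: 3.75 - (-3.75) = 7.5 points. On the log-link scale of the primary model, the ratio of rate ratios is 0.80/1.33 = 0.60.

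The true value is no interaction. The example shows the mechanism under an extreme rule; it is not an estimate.

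**3. How far this depends on the selection rule (simulation, assumed inputs).** There were 98 patients per group (131 x 0.75 = 98.25, after the article's 25% drop-out) and 4,000 runs. The log rate was log(0.15) + log(1.25) if graft + 0.25U + residual with SD 0.5, where U is standard normal vein quality. The rate ratio of 1.25 is the same for everyone, so there is no true effect modification. The probability of a forearm site is logistic in U. For fistulas it is 50% at average vein quality, with slope 1.5. The graft rule is varied. A linear model for the log rate with group, site and their product was tested at two-sided 5%.

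| Graft site rule | Ratio of rate ratios (true 1.00) | Interaction test rejects |
|---|---|---|
| Same as fistula | 1.00 | 5.1% |
| 20% forearm at average vein quality, same slope 1.5 | 1.01 | 5.5% |
| 20% forearm, unrelated to vein quality | 0.77 | 32% |
| 20% at average vein quality, opposite slope -1.0 | 0.62 | 78% |

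The Monte Carlo standard error near 5% is sqrt(0.05 x 0.95/4000) = 0.34 percentage points, so the first two rows are compatible with the nominal level. In the second row, selection shifts both strata in the same direction. It nearly cancels from the interaction, but not from the rate ratio within each stratum.

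**The case against.** The strongest reply is that a post-randomization factor need not bias the test. If surgeons choose site by the same prognostic rule in both groups, or if only the forearm share differs, the interaction test keeps close to its nominal 5%, as the first two rows of the table show. The article does not say how surgeons choose site or how often surgery is missed. A reader might infer that the test is confounded, or that any site interaction is nothing but vessel quality. The documents do not support that: they show that protection is absent, not that bias is present. This part of the reply stands.

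It is also fair that the analysis is labelled exploratory and that one cofactor of six is affected. A reader might infer that participants without surgery fall out of the intention-to-treat analysis. They do not, because the primary outcome runs from randomization whether or not surgery takes place. They are missing only from the site model.

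The reply does not rescue the test as written. Nothing in the article requires site to be chosen alike in the two groups, and the discretion given to the surgical team allows it to differ. The trial data alone could not show that selection was equal with respect to unmeasured prognosis.

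**Conclusion.** The point holds in a limited form. The sequence of randomization, disclosure and vessel choice is stated in the article and needs no assumption. The fistula-graft comparison within forearm or arm strata is therefore not protected by randomization and may be biased. Bias in the interaction requires site choice to depend on prognosis differently in the two groups. Its size is unknown: the rejection rates of about 5% to 78% and the 7.5-point example follow from assumed rules and should not be quoted as expected values. The primary analysis, the safety comparison and the sample size are untouched.

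The same section makes heterogeneity testing conditional: "We will test for heterogeneity of treatment effect as a follow-on exploratory analysis whenever a main treatment effect is detected". A reader might infer a second error here, that the condition would hide opposite subgroup effects. The article does not support calling it one. It expects effects to vary but does not predict reversal, and a later sentence in the section announces the subgroup analyses without repeating the condition. Restricting exploratory tests also limits false positives: six independent tests at 5% give 1 - 0.95^6 = 26.5% for at least one. That is a trade-off for the trial team and no part of this point.

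**What to change.** Define this subgroup by a single pre-specified baseline variable. One workable choice is the site the surgeon would plan for a fistula, recorded for every participant, whichever access is later assigned, at the suitability evaluation for inclusion criterion 8 and before randomization. The plan must say which planned site defines the stratum: recording one for each access type gives two variables and up to four combinations. The field should not be filled in retrospectively once allocation is known.

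If this is not done, remove actual site from the interaction tests and report it only descriptively within each randomized group.

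The cost is one field on the screening form and a sentence or two in the plan; the surgeon's freedom to choose vessels is unchanged. There are two downsides. Enrollment began in June 2022, so participants already enrolled without the field cannot contribute to this subgroup test, and the article does not let their number be worked out. The test would also address planned site, which may differ from the site used.
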